### 2.2. Recruitment of Participants

The study adopted convenience sampling and selected community-dwelling older adults willing to participate in the study in Chiayi County and Yunlin County in Taiwan.

Inclusion criteria are (a) age 60 years or older, (b) ability to speak and understand Chinese, and (c) voluntary participation in the activities of this course. Exclusion criteria were (a) severe chronic diseases (such as heart disease, end-stage kidney disease, cancer) or severe illness, among others, which mean that older adults cannot exercise; (b) severe visual and hearing impairments or using assistive devices without communication barriers; (c) severe bone and joint diseases (e.g., severe osteoporosis, severe knee, or shoulder joint degeneration); (d) arrhythmia requiring drug treatment or a cardiac pacemaker; and (e) severe cognitive impairment (clinical dementia rating ≧ 1) [29].

## 3. Outcome Measures and Measurement Procedures

The primary and secondary outcomes will be assessed at baseline, immediately post intervention, and 3 months post intervention (Table 1).

### 3.1. Description of Outcome Measures

#### 3.1.1. Baseline Measures

Baseline data will include age, sex, education, marital status, residency status, and the experience of one or more events. Most of these data will be assessed through face-to-face interviews with patients in their homes. Data routinely documented by the respective home care services were collected during visits to the home care services.

##### Chronic Disease and Health Problems

The research tools refer to the ‘Chronic Disease and Health Problems Scale (CDHPS) edited by Pao-Hsia Pan (2012) [30]. There are 21 chronic diseases and health problems identified. Respondents were asked to self-evaluate their chronic diseases and the number of symptoms of health problems and to explore the severity of chronic diseases and health problems that interfere with daily life. The scoring method for the severity of interference was 0 points for ‘no inconvenience’, 1 point for ‘slight inconvenience’, and 2 points for ‘slight inconvenience’. The total score ranged from 0 to 42 points.

#### 3.1.2. Primary Outcome

##### Frailty

Frailty was assessed using the Taiwanese Tilburg frailty indicator (TFI-T) [31]. It is divided into three parts with a total of 15 items. The first part measures physical frailty (score range 0–8 points), including unexpected weight loss, physical fitness, difficulty in walking, balance, visual problems, hearing problems, hand strength, and physical fatigue. The second part assesses mental frailty (score range 0–4 points), including cognition, depressive symptoms, anxiety, and coping abilities. The third part is social-level frailty (score range 0–3 points), including living alone, social relationships, and social support, with 0–1 point for each question and a total score of 15 points. The higher the score, the more severe the frailty. The cut-off score of the frailty problem measured using the TFI-T for older adults in the Taiwanese community is 5.5 points, and a score above 5.5 is defined as frailty. The tool has good reliability and validity [31].

#### 3.1.3. Secondary Outcomes

##### Health Function (Physical Function—Senior Fitness Test, SFT)

Physical function concerns the ability of subjects to perform daily activities independently without excessive fatigue and safety concerns (such as climbing stairs easily, walking, bathing, changing clothes, taking care of meals, shopping, and the flexible use of wheelchairs), and the aim was to detect the muscles of the elderly strength, muscular endurance, cardiorespiratory endurance, body flexibility, balance, coordination, and reaction time. The Senior Fitness Test was used to assess the motor skills of older adults [32]. This test assessed strength, flexibility, balance, and endurance [33,34]. It includes the following tests: chair sit-and-reach test, back scratch test, chair stand test, The Biceps Curl Test, 8-foot up-and-go test, and 2 min step test [35]. Currently, the STF tool is widely used in many countries to assess the physical function of older adults. It has been translated into Chinese and other languages and verified for reliability and validity. It can be used by older adults in Chinese culture [34].

##### Health Function (Nutrition—Mini Nutritional Assessment-Short Form, MNA-SF)

The Mini Nutritional Assessment-Short Form has been validated as a screening tool with high sensitivity (97%) and specificity compared with the MNA complete test. The MNA-SF contains only 6 of the original 18 items on the MNA and takes approximately five minutes to execute. The questions concern body mass index, recent weight loss, appetite or eating problems, mobility impairment, acute illness or psychological stress, and dementia or depression. Each question is scored on a scale of 0 to 2 or 3 for an overall MNA-SF score of 14. Patients with a score of 12–14 have normal nutritional status, and those with a score of ≤11 are at nutritional risk or malnutrition [36,37].

## 4. Therapeutic Intervention

### 4.1. Study Protocol

This protocol employs relevant standard protocol items for clinical trials according to the SPRTI 2013 statement (Supplementary File S2).

### 4.2. Experimental Group

Participants in the experimental group will receive a Frailty Prevention Care Management Program (FPCMP-Old Age Program) for 12 weeks. This intervention included an exercise program (design TRX program) and nutritional education. The main elements of the FPCMP-Old Age Program intervention are outlined below in Figure 2 and Figure 3.

#### 4.2.1. Frailty Prevention Care Management Program-Old Age Program

The Frailty Prevention Care Management Program aligns with promoting frailty prevention among older adults in the community. Experts in nursing, long-term care, sports, and functional fields and scholars designed the FPCMP-Old Age Program. The program mainly refers to Ha and Park (2020) and extends the 12-week FPCMP-Old Age Program development, with 120 min per session two times per week [12] (See Supplementary File S3), scheduled from July 2023 to the end of September 2023.

#### 4.2.2. Session 1: Exercise Program-Total Resistance Exercises (TRX) Program

The main purpose of the Total Resistance Exercises (TRX) program was to improve upper- and lower-limb muscle strength and endurance, body flexibility, and a sense of balance and coordination. The exercise program was carried out with a suspension training system, which can improve core muscle strength and physical fitness, activate more core and stabilizing muscle groups, increase joint stability, and strengthen ligaments [38]. It was suitable for use by groups of all ages [39]. The implementation of TRX was not limited by insufficient resources such as venue space, equipment settings, and teachers, because it can be used in almost all environments, and it was convenient and accessible. The TRX was characterized by two straps hanging from an anchor point. To ensure safety throughout training, it was essential to have an anchor point that supports the body weight [21].

The exercise program of this research was designed in terms of frequency; the group exercise training will be implemented twice a week. In terms of intensity, participants will be reminded to consciously feel their body so that they can feel ‘a little sore, a little tight, but not too tired or too tight. The exercise intensity uses Borg’s Rating of Perceived Exertion (RPE) [39]. Participants in the Total Resistance Exercises (TRX) program will aim to achieve a target RPE of 13 (somewhat hard) while exercising.

All movements must maintain a natural upward extension of the spine, slightly retract the jaw, relax the joints, and keep them natural—the principle of breathing without holding one’s breath. Before implementing the exercise, it was necessary to perform a step-by-step inspection, test the venue equipment, and demonstrate and explain the essentials of the action.

##### Each Course Is Divided into Three Parts

(1)Warm-up: A total of 15 min to relax the muscles of the whole body to achieve the warm-up effect.(2)Main exercise: According to the physical function of older adults, they will start training from the simplest movements and angles, set the pull rope to mild intensity, take 10–20 times for each movement as a group, perform three sets as a group, and complete one group rest for 5 min. The following was a description of the scheduled execution movements: performing upper limb TRX exercises, such as ‘Chest Press’ movements (training pectoralis major, anterior deltoid muscles, and triceps brachii) and ‘Low Row’ movements (training back muscles, rear deltoid, and biceps); performing lower body TRX exercises, as as ‘Squat’ (lower body muscles) and ‘Step Back Lunge’ and ‘Step Side Lunge’ (lower body muscles, stability, balance, single leg stability, and power hip adductors). Further, they will perform the ‘Hip Bridge Pose’ (triceps, core, hip flexors, quadriceps, and hamstrings), ‘Leg Curl’ (biceps and core muscles), and eight other movements [40].

The program was divided into three levels, beginner (5–10 times for each group during the first five weeks), intermediate (10–15 times for group, from the 6th week to the 10th week), and advanced (15–20 times for each group, from the 11th week to the 12th week). However, all participants in this study had comparable ability at baseline; therefore, all participants were started at the beginner level and then moved to intermediate and advanced levels as a group. During the exercise, the number of exercises will be gradually increased according to the participant’s physical condition to improve the participant’s muscular endurance.

(3)Cool down: Relaxing exercise, stretching, and relaxation for 10 min.

#### 4.2.3. Session 2: Nutrition Program

The nutritional intervention course included individual nutritional assessment (3 times), education (14 times), and counseling (8 times) for 40 min each time. The main method was to educate the elderly to increase their intake of calories, proteins, calcium, and vitamins [41], considering the age, sex, height of the participants, body weight, and physical activity to assess caloric needs. Participants received a healthy lunch set with a vegetable and protein plate with four compartments, a bowl for rice and fruit, a glass for milk and juice, and a tablespoon [42]. A colored placemat was used to indicate the amount of individualized food on the tableware, helping participants know that they should consume sufficient rice, protein, fruits, vegetables, milk, and nuts daily [42].

### 4.3. Control Group

Participants in the control group will not receive any specific exercise training (i.e., maintain their usual physical activity).

## 5. Statistical Analysis

### 5.1. Data Analysis

Data processing and statistical analyses were performed using the IBM SPSS software (version 23.0; SPSS, Inc., Chicago, IL, USA) for Windows. The mean and standard deviation were used for continuous data. The number, percentage, and homogeneity of categorical data were tested using the *t*-test, and the chi-square test was used for categorical data. The generalized estimating equation (GEE) was used to analyze the two groups before and after, immediately post intervention, and 3 months post intervention [43]. The consideration for choosing the GEE is to control some possible interference factors, deal with multiple repeated measurements of the same case, and explore the primary interaction among variables [44]. We used simple imputation for missing data, including the last or baseline observation carried forward as close to real time as possible during the study [45].

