However, there is still a lack of knowledge about the effects of sling training in frail older adults. Indeed, so far, there are no published studies on TRX exercise combined with a nutrition program in frailty older adults. Therefore, this study aimed to develop a Frailty Prevention Care Management Program that prevents frailty and improves physical activity and nutrition compared to usual care for community-dwelling older adults. It has three objectives:(1)To develop and implement a program for the Frailty Prevention Care Management Program of community-dwelling older adults;(2)To assess the impact of the intervention regarding frailty (physical, psychologic, and social domain), health function, and nutrition in the two groups (experimental and control group);(3)To assess the impact of the Frailty Prevention Care Management Program intervention regarding frailty (physical, psychologic, and social domain) and nutrition immediately post-intervention and 3 months post intervention in the two groups.

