#### 2.1.2. Preliminary Solicitation of Patients Willing to Participate in the Testing

After the invitation process, the information sheets will be distributed and explained. Those individuals who agree to participate will be requested to provide written informed consent, and subsequently, they will be further screened to identify their eligibility to participate. Through questionnaires, case capital data, frailty status, physical function, nutrition, and other tools for older adults in the community were collected. Primary and secondary study outcomes will be collected for the intervention and control groups at baseline assessment (T0), the week immediately post intervention (T1), and at 3 months post intervention (T2; See Figure 1).

The study protocol was approved by the regional Chang Gung Medical Foundation 202202269B0 (See Supplementary File S1). The study protocolwas registered in the ClinicalTrial.gov-register (NCT05883423).

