### 5.2. Sample Size

The sample size for each arm was calculated using the statistical power of G Power [46]. The parameters applied included (a) an alpha level of 0.05 and (b) a statistical power of >80%. The effect size (ES) is estimated based on previous studies [47]. At least 30 subjects in each group were sufficient. Considering a 20% dropout rate, 36 participants in each group were recruited for the trial, therefore there were 72 participants at baseline.

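### Section 5.1 fills missing TFI-T scores by last or baseline observation carried forward without fixing which, and this can bias the group effect, chiefly at 3 months

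*Protocol article*

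**What the plan says.** The missing-data rule is one sentence in section 5.1 of the protocol article: "We used simple imputation for missing data, including the last or baseline observation carried forward". It names two rules and does not assign either to a visit, an outcome or a pattern of missingness. It is not limited to secondary outcomes, so it covers the TFI-T.

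The filled data then enter the main model: "The generalized estimating equation (GEE) was used to analyze the two groups before and after, immediately post intervention, and 3 months post intervention".

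Three other places determine how much this matters:

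- Objective 3, at the end of the Introduction, asks for the effect on frailty and "nutrition immediately post-intervention and 3 months post intervention in the two groups".
- Section 4.2 says that the experimental group "will receive a Frailty Prevention Care Management Program (FPCMP-Old Age Program) for 12 weeks". Section 2.1.2 places T1 in the week after the programme and T2 three months after it, so T2 is an off-treatment assessment.
- Section 5.2 sizes the trial "Considering a 20% dropout rate", with 36 recruited per group. It does not say when in follow-up the loss is expected.

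**The concern.** Carrying a value forward assumes that nothing changed after the participant was last seen. Objective 3 asks whether something changed between the end of the programme and 3 months later. For anyone lost between T1 and T2, LOCF assumes full persistence of whatever was gained or lost by T1, and BOCF assumes a return to the starting value. Neither is an observation. With about 7 of 36 participants per arm affected (36 × 0.20 = 7.2), the T2 contrast would rest partly on the assumption it is meant to test.

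Because the sentence permits either rule, the choice could also be made after the data are seen. In some plausible situations the two rules give materially different answers.

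Lastly, only the experimental arm is asked to attend two 120-minute sessions a week for 12 weeks (section 4.2.1), so dropout may differ between arms. If frailty worsens generally, carrying earlier and better scores forward flatters the arm that loses more people.

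**Working it through.** **Inputs from the plan.** 36 per arm and 20% dropout (section 5.2); visits T0, T1 and T2 (section 2.1.2); higher TFI-T scores mean worse frailty (section 3.1.2), so a negative difference favours the programme. The observed number at 20% loss is 36 × 0.80 = 28.8, about 29 per arm.

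**Inputs assumed.** The plan gives no TFI-T mean, SD or effect size. An effect of -0.74 SD is used because 0.74 is the standardised difference that 30 per group detects with 80% power in a two-sided t-test at 0.05. The baseline mean is set to 0 and, in cases 1 to 3, the control mean stays at 0. Loss is unrelated to outcome.

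**Formula.** For an arm with mean m1 at T1 and m2 at T2, a fraction a lost after T1 and a fraction b lost before T1, the expected filled-in mean at T2 is

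- LOCF: (1 − a − b)·m2 + a·m1 + b·0
- BOCF: (1 − a − b)·m2 + (a + b)·0

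The rules differ only through a. Where there is no post-baseline score, the last value is the baseline value and the two coincide.

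**Case 1: effect wanes from -0.74 to -0.37, 20% loss in each arm (true T2 effect -0.37).**

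| When loss occurs | LOCF | BOCF |
|---|---|---|
| All after T1 | 0.8(-0.37) + 0.2(-0.74) = -0.444 | 0.8(-0.37) = -0.296 |
| Half after, half before | 0.8(-0.37) + 0.1(-0.74) = -0.370 | -0.296 |
| All before T1 | 0.8(-0.37) = -0.296 | -0.296 |

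LOCF thus runs from 20% too large (0.444/0.37 = 1.20), through no bias, to 20% too small. BOCF is 20% too small throughout.

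**Case 2: effect sustained at -0.74, all loss after T1.** LOCF: 0.8(-0.74) + 0.2(-0.74) = -0.74, unbiased. BOCF: 0.8(-0.74) = -0.592.

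**Case 3: effect grows from -0.37 to -0.74, all loss after T1.** LOCF: 0.8(-0.74) + 0.2(-0.37) = -0.666. BOCF: -0.592. Both shrink it.

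**Case 4: no effect, both arms worsen by 0.5 SD by T2, loss after T1 of 30% (experimental) and 10% (control).**

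- BOCF: 0.7(0.5) − 0.9(0.5) = -0.10 SD, a false benefit.
- LOCF: −(0.30 − 0.10) × (worsening after T1). This is -0.04 SD if 0.2 SD of the worsening falls after T1, and -0.05 SD if half of it (0.25 SD) does. A simulation gave -0.038.
- Swapping the dropout rates reverses the signs. With equal dropout both biases are zero.

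**Simulation of case 1, all loss after T1** (36 per arm, SD 1, correlation 0.6 between visits, 20,000 runs): observed data -0.368 (SE 0.235), LOCF -0.443 (SE 0.211), BOCF -0.296 (SE 0.189). A separate run of the same pattern on another scale (SD 2, effect -1.5 waning to -0.75) rejected the null in 55% of trials under LOCF, against 34% under BOCF and 34% with observed data.

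**The case against.** The strongest reply is that the consequences depend on circumstances the plan does not describe. Most of that stands, and it rules out several stronger readings.

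- *A reader might infer that choosing LOCF or BOCF by itself sets the direction of the bias.* It does not. If dropout happens mainly during the programme, which the attendance burden makes plausible, the two rules nearly coincide and both are conservative for a real effect in the cases above. The 20% overstatement is the extreme in which all loss follows T1 and the effect halves.
- *A reader might infer that carry-forward distorts the group contrast whenever means change over time.* With no effect and equal dropout, a common decline cancels between arms. Simulated bias was about zero and type I error about 5% under both rules.
- *A reader might infer that the standard errors are understated.* Carry-forward SEs are 10% (LOCF) to 20% (BOCF) below the observed-data SE, but they match the estimators' own sampling spread (LOCF 0.212 reported and 0.212 actual; BOCF 0.189 and 0.190). The trouble is precision around a shifted target.
- *A reader might infer a materially inflated type I error.* About 8% for BOCF arises in case 4, which needs both a 0.5 SD worsening in roughly six months and 30% against 10% dropout. Neither figure is in the plan. With a 0.15 SD worsening the BOCF bias is 0.2 × 0.15 = 0.03 SD and the error rate about 5.4%.
- *A reader might infer that the GEE needs no missing-data method.* It accepts incomplete records, but without weighting it generally requires data missing completely at random.

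An unseen analysis plan may add sensitivity analyses. That would not change the primary method, which section 5.1 states outright and nothing else in the article limits.

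**Conclusion.** The concern holds as a defect in a stated method. Section 5.1 commits to single imputation by either of two carry-forward rules, leaves the choice open, and applies it to the primary outcome in a trial that plans for 20% loss. The effect chiefly exposed is the T2 contrast in objective 3.

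How large the bias is, and which way it runs, cannot be read from the documents. In the waning case it ranges from 20% overstatement to 20% understatement under LOCF, according to when people leave, and is 20% understatement under BOCF. With a sustained effect and all loss after T1, LOCF is unbiased and BOCF shrinks the effect by 20%. With general worsening and unequal dropout, both rules favour the arm that loses more people even when there is no effect: about 0.04 SD for LOCF and 0.10 SD for BOCF under the values assumed in case 4. All these sizes rest on assumed trajectories and on dropout unrelated to outcome; the 20% is the plan's only contribution.

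**What to change.** In section 5.1, drop carry-forward as the primary method. Analyse all observed T0, T1 and T2 values with a likelihood-based mixed model containing group, time and group by time, and state that it is valid under missing at random.

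If the GEE is to be kept, precede it with multiple imputation using a small model: T0 and T1 TFI-T, group, age and sex. A larger model fitted separately by arm, adding CDHPS, the six SFT tests and MNA-SF, would put a dozen or more predictors on about 29 observed participants per arm and is best avoided. The mixed model is the simpler choice here.

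Keep at most one carry-forward rule, named in advance, as a labelled sensitivity analysis.

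The cost is one rewritten paragraph, a little more analysis work and somewhat wider intervals. In the simulation, the SE from observed data alone was 0.235, against 0.211 under LOCF and 0.189 under BOCF.

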### 5.2. Sample Size

The sample size for each arm was calculated using the statistical power of G Power [46]. The parameters applied included (a) an alpha level of 0.05 and (b) a statistical power of >80%. The effect size (ES) is estimated based on previous studies [47]. At least 30 subjects in each group were sufficient. Considering a 20% dropout rate, 36 participants in each group were recruited for the trial, therefore there were 72 participants at baseline.

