## 2. Materials and Methods

This quasi-experimental and single-blinded trial with a non-equivalent control group uses a before-after design. The FPCMP-Old Age program trial will take the form of a non-randomized, two-group (experimental and control group) trial, with repeated measures at three time-points to improve the community effects of different levels of frailty, health function, and nutrition (Table 1). Cluster RCTs are increasingly used, particularly in primary care research [28], in which groups of participants rather than individual participants are randomized. However, practical challenges remain, such as an increased sample size and complex recruitment procedures. Due to time and resource limitations, this study did not choose to use cluster RCT at the level of communities.

When collecting research samples, the “community” was deliberately used as the unit of collection. Considering that this study recruits four units (including the experimental group and the control group), community units need to be involved. The experimental group and the control group cannot be recruited from the same unit, and this study is prone to contamination problems. Another reason why this study cannot use random assignment is to consider the four community units that received the case. If random assignment is used, there is a chance that strongholds with better or worse functionality will be assigned to the same group (experimental group or control group). Therefore, this study adopts a match to make the health attributes of the two groups of participants close. It was expected that the proportion of control confounding factor allocation will be balanced within the two groups. Therefore, to control or reduce the impact of confounding factors on research, the community was selected, and the experimental and control groups will be recruited from four different communities, but with similar health attributes (Chiayi and Yunlin County).

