### 2.1. Participants and Eligibility

The scope of this study was to accept cases in Chiayi and Yunlin County. Four convenient samples, two experimental groups, and two control groups of people meeting the inclusion criteria will be drawn from four communities, respectively. These four communities are similar in the main aspects, such as population density, economics, and level of community health services. With the support of the local health bureau, the program was accepted by the communities. The research nurses independently completed the data collection, and data collection was completed through one-on-one interviews.

The participants could not be masked after allocation because of the nature of the intervention. The research nurses were similarly not masked because they had to allocate patients to the experimental group and monitor the integrity of the intervention. This study blinded the athletic trainers and did not know that which community participants were the experimental group, because athletic trainers had no role in recruitment, outcome assessment, or data analysis for this study.

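### Arm is fixed by community, two per arm, but neither the sample size nor the stated reasons for the GEE allow for it; the claimed power and 5% error hold only if change does not vary between communities

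*Protocol article*

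**What the plan says.** Section 2 makes community the unit of collection and rules out recruiting both arms from the same unit. Section 2.1 says that two experimental and two control samples "will be drawn from four communities, respectively". Section 4.2.2 delivers the exercise as group training twice a week, to the experimental arm only.

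Section 2 considers a cluster-randomised design, notes that "practical challenges remain, such as an increased sample size and complex recruitment procedures", and sets it aside for lack of time and resources.

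Section 5.2 sizes the trial from "an alpha level of 0.05", "a statistical power of >80" per cent, and an effect size described only by "The effect size (ES) is estimated based on previous studies". It concludes "At least 30 subjects in each group were sufficient" and then "Considering a 20% dropout rate, 36 participants in each group were recruited for the trial". No ICC or design effect appears.

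Section 5.1 gives three reasons for the GEE: to control possible interfering factors, to "deal with multiple repeated measurements of the same case", and to explore interactions. Community is not named as a cluster, a level or a covariate.

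**The concern.** People in one community share its leaders, local activities and, in the experimental arm, the training sessions. The article gives its own grounds for expecting this to matter. Section 2 worries that better- or worse-functioning sites could fall in the same arm. The Introduction chooses group delivery because it promotes social participation and relationships, and the primary outcome, TFI-T, scores social relationships and support.

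If mean change differs between communities for reasons other than the programme, that difference is part of the arm comparison. A person-level standard error omits it, so p-values come out too small and any intervals too narrow. With two communities per arm there is little information with which to separate a programme effect from a community effect. At stake is the false-positive rate on the primary outcome and the meaning of the stated power.

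**Working it through.** **Inputs from the article.** Alpha 0.05; power above 80%; 30 per arm before dropout; 20% dropout; 36 per arm recruited; two communities per arm (sections 2.1 and 5.2).

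**Assumed, because not printed.** A two-sided two-sample t-test; equal community sizes, so 30/2 = 15 analysed per community; an ICC of the change score from 0.01 to 0.10.

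**1. The plan's own figure.** The 30 cannot be reproduced forwards without an effect size. Solving backwards for 80% power with 30 independent people per arm gives a standardised difference d = 0.736. Other readings also fit 30: d = 0.65 for a one-sided t-test, or a repeated-measures F test with f of about 0.13 to 0.33, depending on the correlation and the effect tested. The step to 36 is 30 × 1.2 = 36. All of these treat people as independent.

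**2. Design effect.** DE = 1 + (15 − 1) × ICC. For example, at ICC 0.05, DE = 1 + 14 × 0.05 = 1.70.

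**3. Type I error when community is ignored.** Approximately 2 × [1 − Φ(1.96/√DE)]. At ICC 0.05: 1.96/√1.70 = 1.503, giving 13.3%. This was checked by simulating four communities of 15 with no programme effect. It does not depend on d.

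**4. Valid community-level comparison.** A t-test on two versus two community means has 2 degrees of freedom and a critical value of 4.30. Its noncentrality is d × √(15/DE). At ICC 0: 0.736 × √15 = 2.85, giving 36% power.

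| ICC | DE | Type I error, formula | Type I error, simulated | Noncentrality | Community-level power |
|---|---|---|---|---|---|
| 0 | 1.00 | 5.0% | 5.1% | 2.85 | 36% |
| 0.01 | 1.14 | 6.6% | 6.6% | 2.67 | 33% |
| 0.02 | 1.28 | 8.3% | 8.4% | 2.52 | 30% |
| 0.05 | 1.70 | 13.3% | 13.3% | 2.19 | 25% |
| 0.10 | 2.40 | 20.6% | 21.1% | 1.84 | 19% |

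**5. No dropout.** With 36/2 = 18 analysed per community, the type I error by formula is 7.0%, 9.0%, 15.0% and 23.3% at the four non-zero ICCs. The community-level power at ICC 0 is 41%. The picture does not change.

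**6. What the person-level test would show.** In the same simulation with d = 0.736 and 15 per community, it rejects in about 79%, 78%, 75% and 72% of runs as the ICC rises from 0.01 to 0.10. The rejection rate falls only modestly; the main damage is to the error rate. A high rejection rate from a test whose size is 13% or 21% is not valid power at the 5% level.

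**The case against.** The strongest reply is that the damage is conditional. The article gives no ICC, and at ICC 0 the person-level calculation stands. At ICC 0.01 the type I error is only about 6.6%. The effect size and test are also back-solved. All of this is right: the direction is firm, the size is not.

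A second reply is that the article is condensed and an analysis plan may specify the GEE further. Section 5.1 names no subject variable or working correlation, and it gives interfering factors and interactions as reasons besides repeated measures. So one cannot say that the GEE is justified by repeated measures alone, or that it certainly ignores community. What stands is that the only correlation mentioned is within person, and that section 5.2 states its full list of inputs without clustering.

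A third reply is that section 2 matches communities on health attributes, and that the limitations in section 6 admit confounding. Matching may narrow the differences, but it does not remove within-community correlation, and section 6 does not mention clustering.

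Three stronger readings are tempting but not supported:
- **That the power and p-values are simply invalid.** They are valid if there is no between-community variation, and the article neither shows nor excludes that.
- **That section 2 claims not randomising saves sample size.** It lists the larger sample among the challenges of a cluster trial and gives time and resources as its reason; the saving is at most implied.
- **That whole communities are trained as groups in both arms.** Participants are volunteers from convenience samples, and controls receive no training.

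**Conclusion.** The point holds in conditional form. Arm is fixed by community with two communities per arm, section 5.2 makes no allowance for this, and section 5.1 does not name community. The power above 80% and the nominal 5% error therefore rest on an unstated assumption of no between-community variation in change.

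For ICCs of 0.01 to 0.10 a person-level test would have a true type I error of roughly 7% to 21%. A comparison that respects the four communities would have at most about 36% power with 30 analysed per arm. These sizes rest on the assumed ICC range and equal communities; the power figure also rests on a two-sided t-test with d of about 0.74.

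The defect is wrong as written rather than merely incomplete, because the power statement is unqualified and bears on the primary outcome.

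**What to change.** - **Section 5.2:** state that power above 80% assumes independent participants with no between-community variation. Add that a community-level comparison of two versus two has at most about 36% power at the same effect with 30 analysed per arm, and give the effect size and test used.
- **Section 5.1:** show the four community-specific changes in TFI-T and report the community-level comparison of the four mean changes (2 df) beside the GEE. Describe the GEE p-values as conditional on no community effect. Do not rely on a sandwich variance clustered on four communities, which is unreliable with so few. A random community-by-time term would be poorly estimated for the same reason.
- **Section 2:** add that the sample-size increase named for cluster trials comes from assigning whole communities and so applies to this design too.
- **Conclusions:** treat the comparison as exploratory and limit it to these four communities.

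**Cost:** wording and one simple extra analysis, with no extra participants. The stated power becomes less favourable, the community-level interval will be much wider, and the conclusion is narrower. These changes make the limit visible but do not remove it. Only more communities per arm would do that, and the programme was scheduled for July to September 2023, before the article was published.
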